# BAck iN the Game (BANG) – a smartphone application to help athletes return to sport following anterior cruciate ligament reconstruction: protocol for a multi-centre, randomised controlled trial

**DOI:** 10.1186/s12891-020-03508-7

**Published:** 2020-08-08

**Keywords:** Return to play, Knee, Rehabilitation, Telemedicine, Mobile health

## Abstract

**Background:**

Sustaining injury is a common consequence of playing sport. At least one in every three recreational athletes with anterior cruciate ligament (ACL) reconstruction do not return to their preinjury sport following treatment. Psychological factors including confidence and fear of new injury exert large effects on returning to sport. The primary aim of this trial is to test whether a custom smartphone application delivering cognitive-behavioural therapy is effective for improving the number of people who return to their preinjury sport and level following ACL reconstruction.

**Methods:**

Participants scheduled for primary ACL reconstruction are recruited prior to surgery from one of six trial sites in Sweden. We aim to recruit 222 participants (111 in each group) for the BANG trial. Participants are randomly allocated to receive either usual rehabilitation care alone or usual rehabilitation care plus the Back in the Game smartphone application intervention. Back in the Game is a 24-week Internet-delivered programme, based on cognitive-behavioural therapy. The primary outcome is return to the preinjury sport and level at 12 months follow-up. The secondary outcomes assess physical activity participation, new knee injuries, psychological factors, quality of life and physical function. Physical activity participation and new injuries are self-reported every two weeks for 12 months, then every 4 weeks to 24 months follow-up. Psychological readiness to return to sport, knee self-efficacy, motivation to participate in leisure time physical activity, knee-related quality of life, and self-reported knee function are also assessed at 3, 6, 9, 12 and 24 months after surgery. A clinical assessment of strength, knee range of motion, effusion and hopping performance is completed by a blinded assessor at 12 months to assess physical function.

**Discussion:**

This protocol outlines how we plan to assess the efficacy of a custom smartphone application, delivering cognitive-behavioural therapy to address fear, confidence and recovery expectations, for improving return to sport following serious sports-related musculoskeletal injury. The BANG trial employs a pragmatic design to best reflect the reality of, and inform, clinical practice.

**Trial registration:**

ClinicalTrials.gov, NCT03959215. Registered 22 May 2019.

## Background

Regular participation in sport and active recreation is advocated by the World Health Organization as important for improving global physical activity levels [1, 2]. At least one in every three adults do not meet recommendations for the amount of physical activity required for health benefits [3]. Participating in vigorous activities (i.e. sport) may afford greater health benefits than moderate physical activity [4–6]. Therefore, the health benefits of participating in organised sport should not be underestimated. The dilemma is, ill-health – sustaining injury – is a common consequence of playing sport.

Based on register data of serious sports and active recreation injuries, at 1 year after injury, one in three people had leisure time physical activity levels that were below the minimum recommended for health benefits [7]. People who stopped being active were highly active in sport before their injury. It is unclear whether the injury caused the person to quit playing sport. Rehabilitation clinicians often encounter the athlete who has the physical capacity to participate in sport, but is afraid to participate.

Returning to sport is usually the primary concern of athletes following injury. Yet after serious injury, like anterior cruciate ligament (ACL) tear, up to half of athletes do not return to competitive sport [8]. The transition through rehabilitation and back to sport can be difficult for injured athletes as they experience concerns about their ability to perform at the same level as before the injury, and anxiety about sustaining a new injury [9]. Adding to the challenge, is that (i) there is no systematic approach to addressing psychological concerns during sports injury rehabilitation, (ii) rehabilitation clinicians often feel ill-equipped to provide effective psychological support, [10] and (iii) during the time the athletes are returning to sport, they typically lack the support of a rehabilitation clinician, having been discharged from rehabilitation months earlier.

A self-directed, stand-alone intervention, serving as a complement to rehabilitation might be an effective way to overcome some of the barriers to delivering effective psychological support to athletes during, and after, rehabilitation. eHealth technology facilitates low-cost, on-demand delivery of psychological support to injured athletes [11]. Because smartphones are a ubiquitous part of daily life, they are an attractive platform from which to deliver evidence-based strategies for improving confidence to return to sport that athletes can access anywhere, and at any time – psychological support in the athlete’s pocket.

### Aims and hypothesis

The primary aim of this randomised controlled trial is to test whether Internet-delivered cognitive-behavioural therapy to address confidence for returning to sport (Back in the Game app), is effective for improving the number of people who return to their preinjury sport and level following ACL reconstruction.

The secondary aims are to assess the effect of the Back in the Game app on participation in sport, incidence of new knee injuries, psychological readiness to return to sport, knee self-efficacy, motivation to return to sport, knee-related quality of life, and self-reported knee function.

Our hypothesis is that more patients who use the app in addition to receiving usual rehabilitation care following ACL reconstruction will return to their preinjury sport and level than patients who receive usual care alone.

## Methods

The BANG trial is a parallel-group, two-arm, superiority trial. Participants with ACL reconstruction will be recruited from one of six clinical sites and randomly allocated (in blocks of 6 with a 1:1 allocation, stratified for site) to receive either usual rehabilitation care alone (control group) or usual rehabilitation care plus the Back in the Game smartphone application (experimental group) (Fig. 1). The primary outcome is return to the preinjury sport and level at 12 months after surgery.

**Fig. 1 Fig1:**
[figure not shown]
Flow of participants through the trial. Fortnightly physical activity and injury registration in the first year of follow-up, and monthly physical activity and injury registration in the second year of follow-up are not shown

### Study setting

Participants are recruited from three metropolitan private hospitals, one University hospital and three regional public hospitals in southern and western Sweden.

### Recruitment process

The clinic co-ordinator at each site completes eligibility screening of patients who have been scheduled by their treating orthopaedic surgeon for ACL reconstruction. Patients who meet the eligibility criteria are provided written information about the trial. Approximately 5 days later, patients are asked if they wish to consent to participate and be contacted by the trial co-ordinator.

The trial co-ordinator contacts participants via email and short message service (SMS) with information about how to download the app and create an account. A second round of consent to participate in the study occurs at this point – participants must complete electronic informed consent before their app account is registered. Recruitment commenced in June 2019 and is anticipated to conclude in December 2020.

#### Recruitment rate and strategies to achieve adequate participant enrolment

Approximately 4000 ACL reconstructions are performed annually in Sweden; the trial sites perform approximately one third of these surgeries [12]. Patients aged between 16 and 30 years comprise approximately 60% of all patients receiving ACL reconstruction in Sweden [12]. Based on our previous experience, we expect approximately 20 to 40% of patients to be eligible to participate in the BANG trial (typical clinical population varies at the clinical sites – we expect the metropolitan sites will have a higher proportion of potentially eligible patients). We expect approximately 50% of eligible patients to consent to participate in the trial.

We aim to recruit 222 participants (111 in each group) for the BANG trial. Recruitment progress at each trial site is formally reviewed every 6 months to judge the likelihood of completing recruitment according to the planned timeline. If recruitment is slower than anticipated, we will consider approaching additional clinical sites to assist with participant recruitment.

### Eligibility criteria

Participants who meet the following criteria will be included in the trial:
Age 15 years to 30 years at the time of ACL injuryUnilateral primary ACL rupture (diagnosed by clinical examination and/or MRI)Time between injury and ACL reconstruction not more than 12 monthsPlaying contact pivoting or non-contact pivoting sport at least twice per week prior to ACL injuryIntend to return to sport following ACL reconstructionNormal/healthy contralateral kneeFluent in written and spoken Swedish language

Participants with the following will be excluded from the trial:
Medial collateral ligament or lateral collateral ligament injury requiring surgeryPosterior cruciate ligament injuryMeniscus injury and/or treatment requiring alteration to usual rehabilitation careArticular cartilage injury and/or treatment requiring alteration to usual rehabilitation carePrevious ACL injury to either kneeInjury to either lower limb that required medical care during the 12 months prior to index ACL injuryOther injury or illness that could affect knee rehabilitationTaking medication for mental health problems

We recruit young, pivoting sport athletes who desire to return to sport, because the intervention is tailored to address the mental challenges these athletes typically report [13–17]. Participants must have sufficient Swedish language comprehension because the intervention is only available in Swedish. Previous experience of ACL injury, [18] and social and contextual factors, including age and desire to return to sport, [8, 19, 20] may also influence returning to sport. Our eligibility criteria will help minimise the confounding effect of injury history, age and desire to return to sport on the trial results.

### Interventions

The Back in the Game app and usual rehabilitation care are summarised according to the Template for Intervention Description and Replication (TIDieR) Checklist [21] (Table 1). All participants complete post-operative rehabilitation as normal. As part of usual rehabilitation care in Sweden, patients typically receive generic written information about knee injury and surgery, recovery in the early post-operative period, return to sport, and injury prevention. A summary of the typical written information patients receive from their treating clinician is delivered to both groups via the smartphone application. The Back in the Game app intervention delivers additional, tailored information and cognitive-behavioural therapy exercises to complement post-operative rehabilitation.

**Table 1 Tab1:** Overview of usual rehabilitation care (control) and the Back in the Game intervention (experimental). All participants receive usual post-operative rehabilitation care

TIDieR item	Control	Experimental
**Name**	Usual post-operative rehabilitation care	Back in the Game plus usual post-operative rehabilitation care
**Why**	Usual care reflects the real-world clinical context. Rehabilitation helps patients recover from surgery, gradually regain knee function, and prepare to return to sport.	Psychological factors such as confidence and anxiety about new injury, have strong influences on returning to sport after serious knee injury. Rationale: supporting psychological readiness to return to sport, in addition to usual rehabilitation, will help athletes transition back to their sport. A self-directed approach will help target the specific challenges encountered by the individual.
**What (materials)**	Strength training equipment (e.g. free weights, machine weights, resistance bands, suspension cables), balance training equipment (e.g. BOSU ball) and aerobic training equipment (e.g. treadmill, stationary bicycle) as available in the usual care setting.	All content is provided on-demand through the Back in the Game smartphone application (see https://vimeo.com/345486299/6bba07cc11 for an overview [in Swedish]).
**What (procedures)**	Usual rehabilitation care for pivoting sports athletes typically comprises 4 phases [22]: 1. Acute phase aimed at reducing pain and swelling, improving knee movement, and recovering performance of activities of daily living (e.g. walking without aids). 2. Intermediate phase aimed at progressing muscle strength sport-specific tasks 3. Late phase 4. Injury prevention phase The treating clinician and the patient collaborate to decide on the specific therapies and exercises, and the number of face-to-face, home-based and gymnasium-based treatment/training sessions required.	Users receive a notification at least every 2 weeks to complete tasks relevant to their stage of rehabilitation. The intervention is designed to be complementary to patients’ rehabilitation progression. The 24-week programme is based on cognitive-behavioural therapy principles, and comprises 7 modules: 1. Goal setting 2. Confidence for recovery 3. Confidence for return to sport 4. Confidence for performance 5. Confidence to stay injury-free 6. Support to handle thoughts and emotions related to recovery and return to sport 7. Education about knee injury, recovery, return to sport, and safe sports participation
**Who**	Physiotherapist plus patient-directed home and/or gymnasium-based sessions	Patient-directed via custom application
**How**	Typically, individual face-to-face treatment sessions combined with independent sessions at home and/or gymnasium. Some clinicians may provide group rehabilitation sessions.	Internet-delivered (smartphone or desktop application)
**Where**	Swedish outpatient rehabilitation clinic (either public/primary care or private setting) plus home and/or gymnasium-based programme at a convenient location for the participant.	Users access the intervention on-demand via custom application
**When**	The duration of rehabilitation is highly varied. Post-operative rehabilitation programmes typically run for at least 6 months, and usually cease by 12 months.	A 24-week programme commencing one week following ACL reconstruction (i.e. in the first post-operative week). Users continue to have access in ‘read-only’ mode from the end of the active intervention period (24 weeks) up to 12 months following ACL reconstruction.
**How much**	Highly variable. Clinical practice guidelines recommend at least 3–4 sessions per week. In the early post-operative phase, rehabilitation sessions may be short duration and more frequent. In the late phase, rehabilitation sessions may be longer duration (minimum 40 min) and less frequent.	Minimum 30 min recommended training per week over the 24-week programme. Users receive up to 3 SMS reminders per new task.
**Tailoring**	The treating clinician directs rehabilitation content to focus on specific impairments or functional limitations as appropriate for the patient’s daily living and sport demands. We expect the exercises chosen will be highly variable but will cover the 4 broad rehabilitation phases.	Users choose the cognitive-behavioural therapy task they would like to practice each week from a task menu. Intervention modules are tailored to the progression of rehabilitation (e.g. focus on confidence in recovery during the early rehabilitation phase and confidence to perform well in sport during the late rehabilitation phase).
**How well**	Participants record how many sessions per week they attend of face-to-face rehabilitation, and how many home-based and gymnasium-based rehabilitation sessions they complete.	The research team will track use usage statistics.

TIDieR, template for intervention description and replication; ACL, anterior cruciate ligament

#### Back in the Game app

A 24-week programme (Fig. 2) based on cognitive-behavioural therapy principles, and designed to deliver on-demand psychological support targeting the psychological barriers to athletes returning to sport. There are 7 self-directed modules to build confidence to return to sport that are designed to progress in complexity and mirror progress in post-operative rehabilitation.

**Fig. 2 Fig2:**
[figure not shown]
Summary of the Back in the Game intervention. Each row represents a self-directed module. Each dot represents how frequently tasks are delivered to the user

Each module includes a progression of different tasks: short-term and return to sport goal setting, visualisation, relaxation/meditation, exercises to reduce fear, watching interviews with previously injured athletes (plus self-reflection questions), reading information about managing pain and the thoughts and emotions arising during rehabilitation, and developing an action plan for staying confident to return to sport. Users receive notifications to complete new tasks at least each fortnight (Fig. 2).

At the conclusion of the active 24-week intervention period, users have access to all modules and tasks in ‘read-only’ mode; users will not be sent notifications to engage with the intervention after 24 weeks.

#### Usual rehabilitation

Following ACL reconstruction, as per routine clinical practice, all participants are referred to outpatient physiotherapy. Overall treatment aims, content and progression of rehabilitation will follow current clinical guidelines [23]. The choice of specific therapies, exercises and the number of treatment sessions needed to achieve the required treatment aims is at the clinical discretion of the treating physiotherapist.

### Outcomes

The primary outcome is the proportion of participants who return to their preinjury sport *and* participation level at 12 months. The secondary outcomes (Table 2, Additional file 1) are measured at clinically-relevant times, and reflect a biopsychosocial approach to outcome evaluation: patient- and clinician-reported knee function, sports participation and new knee injuries for the biological aspect, psychological readiness to return to sport and self-efficacy for the psychological aspect, adherence to the intervention and/or rehabilitation, and a range of baseline characteristics (Table 3, Additional file 1) for the social aspect.

**Table 2 Tab2:** Summary of secondary outcomes

Measurement variable	Aggregation method	Measurement time point(s)
Sports participation	Number of minutes playing (i) contact, pivoting sports, (ii) non-contact, pivoting sports, (iii) non-pivoting sports	Every 2 weeks to 12-months follow-up; every month from 12 to 24 months follow-up
New knee injuries	Proportion of participants who report a new (i) ACL injury, (ii) meniscus injury, (iii) other knee injury or problem	Every 2 weeks to 12-months follow-up; every month from 12 to 24 months follow-up
Psychological readiness to return to sport	Mean or median ACL-Return to Sport after Injury scale [24] score	3, 6, 9, 12, 24 months
Knee-related self-efficacy	Mean or median Knee Self-Efficacy Scale [25] future domain score	12, 24 months
Motivation to return to sport [26]	Median	3, 6, 9 months
Knee-related quality of life	Mean or median ACL-Quality of Life scale [27] score	12, 24 months
Self-reported knee function	Mean or median International Knee Documentation Committee subjective knee form [28] score	6, 12, 24 months
Self-reported knee function	Mean or median Single Assessment Numeric Evaluation [29]	Every 2 weeks to 12-months follow-up; every month from 12 to 24 months follow-up
Functional knee stability	Frequency of giving way episodes	12, 24 months
Knee effusion	Proportion of participants with stroke test [30] score: 0, trace, 1+, 2+, 3+	12 months
Hopping performance [31, 32]	Mean or median limb symmetry index	12 months
Quadriceps and hamstrings strength	Mean or median limb symmetry index	12 months
Adherence to rehabilitation	Number of sessions completed	Every 2 weeks while completing rehabilitation
Adherence to BANG intervention	Number of completed video and audio sessions	6 months

Limb symmetry index is calculated using the formula: $$ \frac{involved\ limb}{uninvolved\ limb}\times 100 $$; ACL, anterior cruciate ligament

**Table 3 Tab3:** Baseline participant characteristics

Variable	Aggregation
Time from injury to surgery	median (IQR)
Age at injury	mean (SD)
Sex	
Female	n (%)
Male	n (%)
Primary occupation	
Student	n (%)
Desk work	n (%)
Manual work	n (%)
Heavy manual work (e.g. construction)	n (%)
Unemployed	n (%)
Preinjury sports participation	
Contact, pivoting sport	n (%)
Non-contact, pivoting sport	n (%)
Return to sport goal	
Return to same sport	n (%)
Return to different sport	n (%)
Return to sport expectations	
Within 1 month	n (%)
Within 6 months	n (%)
Within 12 months	n (%)
After 12 months	n (%)
IKDC subjective knee form [28] score	mean (SD)
General Self-efficacy Scale [33] score	mean (SD)
Knee Self-Efficacy Scale [25] *Future domain*	mean (SD)
Hospital Anxiety & Depression Scale [34] score	mean (SD)

*IQR* interquartile range, *SD* standard deviation, *IKDC* International Knee Documentation Committee

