#### Secondary outcome measures: *new knee injuries*

Participants self-report any new knee problems that have occurred during the registration period (preceding two weeks). We use an ‘all complaints’ definition of injury [37]. Participants describe the problem, and any diagnosis and treatment received (including the clinician and/or institution where diagnosis and/or treatment was provided).

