#### Missing data

If required, we will use multiple imputation to account for missing data in analyses that cannot handle occasional missing values [42]. If there are missing data for the primary outcome, we will either: (i) substitute from the fortnightly sports participation data, or (ii) use multiple imputation if there are > 15% missing outcome data. If there are missing data for the secondary outcomes, we will use multiple imputation if there are > 15% missing outcome data.

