#### Reclassifying variables

For new knee injuries, we plan to classify the collected data into three dichotomous variables for analysis: (i) new knee problem (based on all complaints), (ii) new ACL injury (either knee), (iii) new knee injury treated with surgery. The trial co-ordinator will check all injury registration reports as they are completed and returned by participants. If additional information (e.g. injury diagnosis and treatment) is required, a blinded researcher will contact the participant by phone or text message, and/or review the participant’s medical record (Additional file 1).

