#### Planned secondary analyses: time-varying analyses

We will compare psychological readiness to return to sport (ACL-RSI), motivation to return to sport, self-reported knee function (SANE and IKDC), sports participation and new knee injury between treatment groups using generalised estimating equations. Group, clinical site, and assessment time point will be included as fixed factors. If baseline values were collected, we will also include the baseline value in the relevant model as a covariate. For continuous variables, we will calculate mean difference and 95% confidence intervals. For dichotomous variables, we will calculate the odds ratio and 95% confidence intervals.

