#### Planned secondary analyses: cross sectional analyses

For self-efficacy (K-SES) and quality of life (ACL-QoL), we will use generalised estimating equations for comparisons at 12 months (model 1) and 24 months (model 2) between treatment groups. Group and current participation in preinjury sport will be included as fixed factors. We will calculate mean difference and 95% confidence intervals. In model 2, we will include the 12-month values as a covariate.

For adherence, we will compare the median number of rehabilitation sessions completed per person (i) with the physiotherapist, (ii) at home, (iii) at a gymnasium between the treatment groups using generalised estimating equations.

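### Injuries and rehabilitation sessions in unreturned fortnightly reports can be lost, and the protocol's repeated-measures model and 15% imputation rule do not reliably correct for this

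*Protocol article*

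**What the plan says.** **New knee injuries.** Table 2 (Outcomes) defines the measure as "Proportion of participants who report a new (i) ACL injury, (ii) meniscus injury, (iii) other knee injury or problem", collected "Every 2 weeks to 12-months follow-up; every month from 12 to 24 months follow-up". The section on new knee injuries gives the recall window: "Participants self-report any new knee problems that have occurred during the registration period (preceding two weeks"). No separate window is given for year 2. Under Reclassifying variables, "we plan to classify the collected data into three dichotomous variables for analysis": any new knee problem, new ACL injury, and new knee injury treated with surgery. On checking, "The trial co-ordinator will check all injury registration reports as they are completed and returned by participants". A blinded researcher may then contact the participant or review the medical record if more detail is needed.

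The time-varying analyses section puts new knee injury into a GEE model: "Group, clinical site, and assessment time point will be included as fixed factors".

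**Rehabilitation.** Participants report two-weekly counts of supervised, home and gymnasium sessions, which Table 2 schedules for as long as rehabilitation lasts. The cross-sectional analyses section states that "we will compare the median number of rehabilitation sessions completed per person", by setting. It names no time factor, denominator or completeness rule.

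**Missing data.** "If there are missing data for the secondary outcomes, we will use multiple imputation if there are > 15% missing outcome data". The protocol does not say whether the 15% refers to registrations, participants or derived variables.

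**The concern.** Both measures are assembled from many short self-reports: 26 in year 1, then 12 to 13 in year 2. Taken literally, a proportion of people who report an injury, or a total of sessions completed, falls as fewer reports come back. An injury in a missed fortnight lies outside the next report's window, and the described record review starts from a returned report. Adverse events (Harms) come by self-report every two weeks in year 1, so they are not an independent backup.

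The section on adverse events treats another serious knee injury as the gravest short-term consequence and accepts that the app could paradoxically raise it. Rehabilitation dose is the main co-intervention a reader would want to compare between arms. If the arms differ in how often they report, both comparisons partly reflect reporting behaviour.

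**Working it through.** The protocol gives no expected return rate, trial injury rate or session total, so there is no stated figure to reproduce. Return shares below are assumptions.

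**Inputs.** Registrations in year 1: 52/2 = 26. Sessions: 3 to 4 per week (Table 1) over about 9 months, or 39 weeks (Harms), giving 3 × 39 = 117 to 4 × 39 = 156. Injury risk for illustration: 20%, the protocol's 1 in 5 second ACL injuries among young athletes who returned to sport.

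**1. Session totals, if only returned fortnights are added.** Apparent total = true total × share returned, with equal true totals.

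| Returned | 117 true sessions | 156 true sessions | Relative gap |
|---|---|---|---|
| 90% v 80% | 105.3 v 93.6 (gap 11.7) | 140.4 v 124.8 (gap 15.6) | 1 − 0.8/0.9 = 11% |
| 90% v 70% | 105.3 v 81.9 (gap 23.4) | 140.4 v 109.2 (gap 31.2) | 1 − 0.7/0.9 = 22% |

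**2. Injury per person, if a participant counts only when the injury is reported.** Apparent risk = true risk × probability that the relevant report is returned.
- True risk 20% in both arms, 90% v 80% returned: 18.0% v 16.0%, odds ratio (0.18/0.82)/(0.16/0.84) = 1.15. At 90% v 70% it is 1.35.
- True 25% v 20% (odds ratio 1.33), 80% v 100% returned: 20% v 20%, odds ratio 1.00. A real excess disappears.

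**3. Injury per returned registration, as in the GEE by time point.**
- Non-return unrelated to injury: the return share cancels, leaving 0.20/26 = 0.0077 per returned registration. A simulation of 200,000 per arm gave 0.0077 at both 90% and 70% returned, so there is no bias.
- Non-return related to injury: suppose the registration that would carry the injury is returned 80% of the time and all others 90%. Then 0.20 × 0.8 / (26 × 0.9 − 0.20 × 0.1) = 0.16/23.38 = 0.0068, about 11% too low. If this happens in one arm only, it creates a difference.

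**4. The 15% trigger under three possible units**, with 90% of registrations returned independently.
- Registrations: 10% missing, so no imputation.
- Participants with a complete year 1: 0.9^26 = 6%, so 94% are incomplete and imputation is triggered. At 95% returned, 0.95^26 = 26% are complete.
- A derived per-person value formed from whatever came back: it always exists, so nothing counts as missing.

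The same data give opposite answers depending on the unit.

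**The case against.** A reader might infer that the plan scores an unreturned report as no injury or zero sessions. Nothing in the protocol says so. The rule for an incomplete series may sit in an analysis plan or in Additional file 1, neither of which is shown, and its absence from an article is not an error. The stated injury model works by time point, where an unreturned registration is a missing observation, not a negative one. That part of the objection stands: with non-return unrelated to injury, step 3 shows no bias.

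A reader might also infer that finished rehabilitation cannot be told apart from silence. That is not supported either. Fortnightly sport, injury and knee-function registrations continue to 12 months, so someone who has finished rehabilitation still returns them.

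Nor is unequal reporting established. Outcome questionnaires carry the same invitation and reminders in both arms (Data collection), and missing responses are chased by text message (Data management plan). Only the experimental arm receives extra task reminders in the same app (Table 1), and notifications stop at 24 weeks. The direction of any difference is open, since more contact could raise reporting in that arm.

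What remains is narrower. Chasing reduces gaps but does not say how the remaining ones enter a per-person proportion or total. The described record review does not reach those who stopped reporting. An athlete with a new injury may well stop answering a return-to-sport app, and that is the case the GEE does not protect against. No time-point model is stated for session totals.

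**Conclusion.** The point holds as a weakness in how two secondary measures are defined and collected. It is not a finding that the plan codes non-return as uninjured or zero. Injuries in unreturned registrations can be lost permanently, and the planned GEE is safe only if non-return is unrelated to injury. The per-person summary and the repeated-measures model also use different units. Session totals can fall with non-response, and this is the stronger half of the point. The 15% rule resolves neither case.

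The size depends on return rates that the protocol does not give. At an assumed 90% v 80%, equal session totals appear about 11% apart (12 to 16 sessions), and equal 20% injury risks counted per person would show an odds ratio of 1.15. With equal return in both arms, step 1 gives no gap in session totals and step 2 leaves equal injury risks equal. The primary analysis is not affected, because it uses neither measure.

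**What to change.** 1. **Injury.** Add one closing question to the 12- and 24-month questionnaires on any ACL injury or knee surgery since the index operation. This recovers events from missed windows for two of the three yes/no variables; minor complaints cannot be recovered this way. Treat participants whose status is still unknown as censored at their last returned registration, not as uninjured. Censoring still assumes that loss is unrelated to injury, so report returned registrations by arm.
2. **Rehabilitation.** Replace the comparison of raw per-person totals with a count model that uses the log number of returned fortnights as offset. Take registrations to 12 months, with zero sessions as a valid answer. The offset assumes that returned fortnights are typical of the person's year. Because rehabilitation tapers, gaps concentrated late in the year would strain that assumption.
3. **Missing data.** State the unit to which the 15% applies.

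The cost is one extra item at two time points, a small change of model and one clarifying sentence. Extending the blinded record review to non-responders in both arms is optional. At the assumed 15% drop-out it would concern about 0.15 × 222 = 33 people.
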